## Abstract

**Introduction:**

Front-line health workers in remote health facilities are the first contact of the formal health sector and are confronted with life-saving decisions. Health information systems (HIS) support the collection and use of health related data. However, HIS focus on reporting and are unfit to support decisions. Since data tools are paper-based in most primary healthcare settings, we have produced an innovative Paper-based Health Information System in Comprehensive Care (PHISICC) using a human-centred design approach. We are carrying out a cluster randomised controlled trial in three African countries to assess the effects of PHISICC compared with the current systems.

**Methods and analysis:**

Study areas are in rural zones of Côte d’Ivoire, Mozambique and Nigeria. Seventy health facilities in each country have been randomly allocated to using PHISICC tools or to continuing to use the regular HIS tools. We have randomly selected households in the catchment areas of each health facility to collect outcomes’ data (household surveys have been carried out in two of the three countries and the end-line data collection is planned for mid-2021). Primary outcomes include data quality and use, coverage of health services and health workers satisfaction; secondary outcomes are additional data quality and use parameters, childhood mortality and additional health workers and clients experience with the system. Just prior to the implementation of the trial, we had to relocate the study site in Mozambique due to unforeseen logistical issues. The effects of the intervention will be estimated using regression models and accounting for clustering using random effects.

**Ethics and dissemination:**

Ethics committees in Côte d’Ivoire, Mozambique and Nigeria approved the trials. We plan to disseminate our findings, data and research materials among researchers and policy-makers. We aim at having our findings included in systematic reviews on health systems interventions and future guidance development on HIS.

**Trial registration number:**

PACTR201904664660639; Pre-results.

Strengths and limitations of this studyThese trials assess the effects of improving paper-based health information systems, which are greatly used particularly in remote, rural areas but which are neglected in research.The paper-based intervention (PHISICC) has been developed using a human-centred design approach, with front-line health workers and designers driving the cocreation process.Despite the complexity of health systems interventions, we have applied robust experimental methods, together with qualitative research, to assess and understand the effects of the paper-based intervention. Robust evidence on health systems is more likely to gain the credibility of policy-makers and to make it into systematic reviews, guidance development and policy and practice.Research targeting front-line health workers in remote, rural areas has to take place where they live and work, which poses serious obstacles in the organisation, management and monitoring of the trials.These obstacles, aggravated by the COVID-19 pandemic, have challenged the mobility of the research team, the availability of the intervention in one of the countries and the duration of the trials.

## Introduction

Front-line health workers (HW) in remote, rural health facilities (HF) in many countries are the first contact with the formal health sector of the population and they are confronted with life-saving clinical and public health decisions on a daily basis. Decisions are made by exerting a balanced judgement on the information related to healthcare events, such as making the correct diagnoses or deciding on which vaccinations a child should receive on a given day. In order to properly handle this information, appropriate data support tools and processes are required, referred to as the health information system (HIS), or routine HIS, or health management information system.^1^ In reality, though, HISs are primarily designed to report aggregated health events to the higher tiers of the health systems rather than to inform decision making at the point of care.^2^

Increasing pressure by donors and governments to collect more and more data has aggravated the situation, through the proliferation of data support tools that have overloaded front-line HWs compromising their capacity to deliver good quality of care and to produce good quality data^3^ for higher level decision making.

Promising ‘quick fixes’, such as the scale up of digital HIS, are taking a long time to implement and face enormous challenges related to infrastructure, equipment and services necessary to run them. Besides, research evidence on the effects of digital solutions remains patchy and inconsistent, even in high-income country settings, where complaints about computerisation of clinical care have been raised,^4^.^5^ Hence, it is very likely that paper tools will remain a primary, if not unique, data support mechanism, particularly in remote, rural HF in many countries.

Paper-based Health Information System in Comprehensive Care (PHISICC) is a multiyear, multicountry, mixed-methods research project that aims at producing and testing an innovative paper-based HIS to improve data quality and use, decision making and health outcomes, at primary healthcare (PHC). It is being carried out in selected areas within Côte d’Ivoire, Mozambique and Nigeria. The project started in 2015, producing a systematic review on the effects of HIS interventions^6 7^ and a framework synthesis on how HIS are understood in the literature in order to learn from past experiences in HIS developments. This global evidence was coupled with studies to characterise the existing HIS in the three countries, to understand how HWs interact with the HIS and to identify entry points for HIS design improvements. With these bodies of evidence the research team was well equipped to engage into a human-centred design (HCD) cocreative process with front-line HW to design an innovative HIS (PHISICC). See figure 1 for an illustration of the structure, processes and evidence flow within PHISICC.

**Figure 1 F1:**
[figure not shown]
PHISICC research programme structure, processes, deliverables and flow of evidence. Timelines are approximate. HIS, Health Information System; PHISICC; Paper-based Health Information System in Comprehensive Care; WS, work stream.

The impact of the PHISICC HIS on data quality and use, quality of healthcare and HW perceptions is being assessed concurrently in rural areas in the three countries. We describe the design of the trial here, consistent with Consolidated Standards of Reporting Trials reporting guidelines^8^ and the extension for cluster randomised controlled trials (CRCT);^9^ see online supplemental file 1.

10.1136/bmjopen-2021-051823.supp1Supplementary data

## Methods

### Aim

The aim of the trial is to address the research question: what are the effects of an innovative paper-based HIS (PHISICC) on data use and quality, quality of health and HW perceptions compared with the current HIS, in rural PHC settings?

### Patient and public involvement

There was no public or patient involvement in the design of the study or selection of study areas because the intervention being assessed in these trials target healthcare providers and decision-makers, rather than patients or the public in general. Population in the catchment area of selected HFs, potentially using their services, were only approached in order to assess the studies outcomes.

On the other hand, we have involved health systems stakeholders and front-line HWs. Ministries of Health (MOH) at several levels participated in the preparation of the research proposal (personal consultations), in the characterisation of HIS that preceded the trials (countries workshops), and throughout all project components (additional workshops, newsletters and personal communications). Front-line HWs in the three countries have cocreated the intervention (ie, paper-based tools) through workshops, personal feedback and piloting under real live conditions. Some of them are part of the research team and coauthoring this manuscript.

### Study design

The study is a CRCT in each of the three countries. In each setting, 70 HFs are randomised to intervention or control (35 per arm). The intervention arm HF use the new PHISICC tools (substituting the usual HIS tools) and the control arm HF use the regular HIS tools. The trial is implemented in the real life contexts of HF carrying out their usual duties.

The trials started between the end of 2019 and beginning of 2020, depending on the country, when the intervention was installed and the baseline surveys carried out. Data collection will last until mid-2021.

### Study areas

MOH officials in several countries were contacted before submitting the proposal to the funding agency in order to explore the willingness to engage in a project focusing on paper-based tools. Officials in several countries rejected the offer on the grounds of upcoming digitalisation plans of the HIS in the country. We partnered with MOH that found the research relevant to their context in three countries.

In each country, the eligibility criteria of study areas were that they had to belong to the operational area of research partners; contain a large enough number of HFs and their catchment population; include vulnerable population (eg, with low vaccination coverage, high childhood mortality); and be comparatively neglected in terms of infrastructure and services. We excluded areas with concurrent research or other types of activities that could conflict with the CRCT (such as the coexistence of another health-related study, massive developments in infrastructure or activities involving migration of the population, such as temporary work sites or changes in working sites) and areas with threats to safety or security that could jeopardise research activities.

The study areas are located in Adzopé, Agboville, Tiassalé and Sikensi districts (Côte d’Ivoire); in Funhalouro, Govuro, Homoine, Inhambane, Inharrime, Inhassoro, Mabote, Maxixe and Panda (Inhambane province, Mozambique) and in Yala Local Government Authority (Cross River State, Nigeria).

### Eligibility of HFs

The intervention is implemented at the HF level. The eligibility criteria of the HF were that they had to be located in the study areas, belong to the governmental health sector and their main activity should be the delivery of PHC services. HFs were excluded if they had specialised clinical services, inpatients, physicians providing care or with plans for staff turn-over.

A ‘master list’ of eligible HFs was prepared based on information provided by the MOH across all study areas. We aimed at selecting 70 of the eligible HF in each country, using simple random techniques in R.^10^ See in figure 2 the selection and allocation trial flow chart.

**Figure 2 F2:**
[figure not shown]
CONSORT diagram: trial flow chart. CONSORT, Consolidated Standards of Reporting Trials; HF, health facilities.

### Allocation and blinding

Allocation of HF into the intervention and control arms took place in a formal event, gathering research partners and MOH officials to offer transparency and promote study ownership by local and national authorities. Equally sized, folded pieces of paper with the names and codes of included HF written on them were introduced in an opaque receptacle where they were manually and blindly mixed. A second receptacle contained two equally sized pieces of paper, one with the word ‘intervention’ and another one with the word ‘control’. A selected person in the meeting, not belonging to the research team, extracted one piece of paper at a time to reach half the number of included HF. Then, a paper was extracted from the second receptacle to assign those HF to the intervention or control arms. The rest of the papers were extracted as well to verify completeness and no duplication of names, and those HF were assigned to the other arm.

Once HFs were selected, all villages or settlements for each health facility catchment area were listed and three in each catchment area were selected. In practice, we selected all villages because the numbers were below (in Côte d’Ivoire) or just above (in Nigeria) the needs. For each village, we used Google satellite maps to identify and geo-locate every visible roof. Where there were many houses per village (roughly, more than fifty or so), a researcher would mark four points in the map slightly beyond the northernmost, southernmost, easternmost and westernmost roofs seen and 30 random points were selected within that square. From the mapped points, 10 per village (with 20 more acting as reserve) were randomly selected and marked on another map used in the field for data collectors to approach households. Where technical problems impeded this approach in a given village, a field supervisor would rotate a bottle on the floor towards the centre of the village and would select at random 10 households in the direction pointed by the bottle, from the outer limit of the village till the centre.^11^

Blinding is only feasible for the research team members carrying out the CRCT data collection and the analyses of the CRCT findings. The intervention (ie, paper tools) are by design very different from the existing system and it is not possible to blind participants or principal researchers.

We already had the agreement of the MOH and selected HF compliant with the inclusion criteria were provided with the intervention shortly after completing the baseline data collection. Therefore, recruitment as such took place at the same time of the allocation of HF into intervention and control arms.

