### Sample size calculations

The required sample sizes for each primary outcome were determined using simulation to incorporate the clustering (table 1) and to take the baseline and end-line surveys into account. Briefly, we simulated 1000 trials with variation between them caused by drawing different samples from the same distributions. We then used the regression models detailed in the data section to analyse each of the simulated trials and estimate the power as the proportion of trials which detected the effect of the intervention as significant. The simulation code was written in R (online supplemental files 2 and 3).

10.1136/bmjopen-2021-051823.supp2Supplementary data

10.1136/bmjopen-2021-051823.supp3Supplementary data

For each country, we require the probability of α, a type I error (rejecting the null hypothesis when it is actually true) to be less 0.05 and the power to be at least 80%.

For vaccination adherence, using a sample size of 35 HF per arm, we would have 80% power in each country to detect as significant a difference between a proportion of due vaccines given from 75% in the control to 85% in the intervention arms, assuming one child per household, 30 households per HF and a between-HF variation equivalent to a k of 0.25, where k is equal to the SD divided by the mean. The value of k is unknown, but was chosen in line with general observations by Hayes and Bennett.^20^

For data quality outcomes, with 35 HF per arm we would be able to detect as significant a difference from a ratio of 0.7 (reported:recorded) vaccinations in the control arm to 0.8 with the intervention with 80% power, assuming 100 recorded vaccinations per HF and an SD of 0.25 in the ratios between HF.

In terms of diagnostic scope, we would be able to detect an increase in the proportion of child visits with more than one diagnosis from 30% to 35% with 80% power with 35 HF per arm, 60 records per HF and assuming a k of 0.25.

We would be able to detect as significant an increase from 50% of treatments having a corresponding appropriate diagnosis to 60% with 80% power assuming 35 HF per arm, 1 treatment per child, 25 children per HF and variation between HF corresponding to k=0.25.

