For the outcome related to HWs’ satisfaction, we would be able to detect as significant an increase from 50% of HWs satisfied to 75%, with 80% power assuming 35 HF, three HWs per HF and a variation between HF equivalent to k=0.25. Since this variable is measured in the end-line survey only, we used the formula in Hayes and Bennett.^20^

In summary, in each country we require 35 HF per arm, 3 HW per HF, 100 vaccination records per HF, 60 sick child records per health facility and 30 children per health facility catchment area.

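### In Côte d'Ivoire the written sampling rule gives fewer than 30 households per facility on average, so the stated size and 80% power for vaccination adherence do not describe that country

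*Protocol article*

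**What the plan says.** All of this is in the protocol article.

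- **Allocation and blinding, villages.** Three villages were to be taken per catchment. The text then reports: "In practice, we selected all villages because the numbers were below" what was needed in Côte d'Ivoire, and just above it in Nigeria.
- **Allocation and blinding, households.** From the mapped points, "10 per village (with 20 more acting as reserve) were randomly selected". The fallback for villages with technical problems (the rotated bottle) also takes 10 households and mentions no reserve. Nothing raises the number per village where a catchment has fewer than three.
- **Sample size calculations, target.** In each country the type I error is "to be less 0.05 and the power to be at least 80" per cent.
- **Sample size calculations, vaccination adherence.** The claim reads "using a sample size of 35 HF per arm, we would have 80% power in each country". The effect is a rise from 75% to 85% of the vaccines due, and k is set at 0.25. Cluster size enters as "assuming one child per household, 30 households per HF". The closing summary requires, again in each country, "60 sick child records per health facility and 30 children per health facility catchment area".
- **Data analysis.** The effect is the arm-by-survey interaction, so baseline and end-line precision both count.
- **Ethics and dissemination.** The Mozambique household survey was cancelled.

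**The concern.** The article states an operating rule, reports that its premise failed in one country, and keeps the target that depended on the premise. The three statements cannot all hold for Côte d'Ivoire.

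Vaccination adherence is the first primary outcome. Household-level measurement is also the article's stated protection against bias from using the health information system both as intervention and as data source. With the Mozambique survey cancelled, Côte d'Ivoire is one of only two countries supplying household evidence. A null result there would be read against a claimed 80% power that the written rule does not deliver. The power statement gives no margin above the 80% minimum.

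This is separate from whether a sampled household contains an eligible child. Here the number of households itself falls short.

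**Working it through.** **1. Reproduce the planned cluster size.** 3 villages × 10 households = 30 per HF, an exact match. With 70 HF this is 70 × 3 = 210 villages and 2,100 households.

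**2. Apply the same rule with fewer villages.** One village gives 10 households (67% fewer) and two give 20 (33% fewer). If the shortage refers to each catchment, affected catchments are at 10 or 20. If it refers to the country total, there are fewer than 210 villages at 10 each, so fewer than 2,100 households. The mean is below 30 on either reading. The bounds are 1,400 households if every HF had two villages and 700 if every HF had one.

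**3. Try to reproduce the stated 80%.** It came from simulation code in supplements that are not shown. Inputs: 35 HF per arm, 75% and 85%, k = 0.25, two-sided 5% (sidedness is not stated).

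| Model | 30 per HF | 20 per HF | 10 per HF |
|---|---|---|---|
| End-line only, Hayes-Bennett formula | 49% | 47% | 41% |
| Change from baseline, HF effect cancels, one observation per household | 97% | 89% | 61% |
| Simulated change, persistent HF effect, one vaccine per child | 82% | 68% | 42% |
| As above, 8 vaccines per child | 98% | 89% | 62% |

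The second row uses SE = √[(3 × 0.75 × 0.25 + 0.85 × 0.15)/(35m)] = √[0.69/(35m)], which is 0.0256, 0.0314 and 0.0444 for m = 30, 20 and 10. Power is Φ(0.10/SE − 1.96). The simulated rows cap facility proportions just below 1, which shrinks the effect somewhat. If HF effects are correlated only 0.8 between surveys, the one-vaccine simulation gives 53%, 44% and 31%.

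The stated 80% lies inside this range and is not shown to be wrong. No single row can be taken as the plan's model.

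**4. Calibrate to the stated 80% at m = 30.** Let f be the share of the variance that scales with 1/m; the article does not give it. Then power = Φ(2.80/√(1 − f + f × 30/m) − 1.96).

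| f | 20 per HF | 10 per HF |
|---|---|---|
| 1 | 63% | 37% |
| 0.5 | 71% | 51% |
| 0.25 | 75% | 63% |

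A milder case: if half the facilities had 20 and half had 30 (mean 25, so 30/m = 1.2), power is about 72% for f = 1 and 78% for f = 0.25.

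**5. What topping up only end-line recovers.** In the cancelling model the variance is 0.375/(35 × m at baseline) + 0.315/(35 × m at end-line).
- Baseline 10, end-line 30: 0.375/350 + 0.315/1050 = 0.00137. SE is 0.037 and power about 77%, against 61% without the change.
- Baseline 20, end-line 30: 0.375/700 + 0.315/1050 = 0.00084. SE is 0.029 and power about 93%, against 89%.

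**The case against.** The strongest reply is that the article never gives village counts per facility. A reader might infer that every Côte d'Ivoire facility had fewer than three villages, and so 10 or 20 households. The text does not say that. Some catchments may have had three or more villages, and the mean could be only slightly below 30. This stands, and it limits the size of the problem. It does not remove it, because on either reading the mean is under 30.

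A second reply is that the 20 reserve points may have been used to top up, under a field rule that an article would leave out. That is possible. But the article calls them a reserve, gives no such use, and mentions none for the fallback method. If they were used, one sentence would settle the matter.

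Third, a reader might take 89% and 61% as the power actually achieved. The documents do not support this. That model gives 97% at 30 households where the plan states 80%, and it applies the shortfall to every facility. It also treats each household as one observation, although the outcome counts several vaccines per child.

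Two further inferences fail. Nigerian catchments above 30 households do no evident harm. Smaller clusters where villages are few are not in themselves a bias: allocation is by facility, and the random-effects models accommodate unequal cluster sizes.

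**Conclusion.** The point holds for household outcomes in Côte d'Ivoire. The written rule gives a mean below 30 households per HF, so neither that figure nor the 80% power for vaccination adherence describes this country.

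The loss of power is real in direction but undetermined in size. The calibrated ranges (63-75% with 20 at every HF, 37-63% with 10 at every HF) assume that the stated 80% is right at 30, that a quarter to all of the variance scales with 1/m, and that all facilities are affected. The share affected is not given. A shortfall in only a few facilities would cost little, and the documents do not show a failed design. Under-5 mortality and client experience draw on the same household sample, but the article states no power for them.

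**What to change.** 1. **Report and restate.** For Côte d'Ivoire, replace 30 households per HF with the number sampled at baseline, giving villages and households per facility. Say whether reserve points were used to top up. Rerun the existing power simulation with the achieved cluster sizes and state the result for that country separately. This needs only data already held and a rerun of existing code.

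2. **Where feasible, set the end-line quota per catchment.** Take 30 households split over the existing villages: 10 each from three, 15 each from two, 30 from one. Use the reserve points already mapped.

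The second step has costs:
- It recovers only part of the precision, because baseline is fixed and the effect is an arm-by-survey interaction. With 10 at baseline and 30 at end-line, even the optimistic model reaches only about 77%.
- The quota would differ between surveys, which the report should state.
- More households per village add some within-village similarity.
- Taking 30 from one village uses all 10 + 20 points and leaves no reserve for non-response. Villages sampled by the fallback method may have no mapped points.
- The household count stays within the 30 per HF that the design assumed, but the article gives no field budget against which to judge the cost.
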